**Fig 3 pone.0294822.g003:**
[figure not shown]
Cohort creation diagram. DOAC: direct oral anticoagulant. *Intention to treat analysis.

To counteract the risk of selection bias when comparing the benefits of different treatments against the reference treatment (acenocoumarol), cohorts will be compared by matching individuals or patients based on their propensity scores (PS) for acenocoumarol versus each of the four DOACs and versus warfarin.

Measurement of medication effect or outcome for both effectiveness and safety variables will take into account the first recorded event (effectiveness or safety) among those included in the study.

The reporting of this study will abide by the Strengthening the Reporting of Observational Studies in Epidemiology (STROBE) statement for cohort studies [19].

### Registration details

The study protocol was submitted to the Spanish Agency of Drugs and Health Products (SADHP, the competent authority) and classified as an “Observational study” (SADHP number: 0004-2022-OBS; 12 January 2022).

## Ethics and dissemination

The study was approved by the Andalusian Biomedical Research Ethics Coordinating Committee (ABRECC), which considered that it complied with the ethical principles established for this type of study as set out in the Declaration of Helsinki (26 May 2020).

The results will be presented at national and international conferences and published in high impact journals.

### Project Data Protection Impact Assessment (DPIA)

A DPIA was required to obtain authorisation of the study by the ABRECC. This tool assesses the potential risks to which the processing of personal data may be exposed during the conduct of the study, and the provision of possible interventions or safeguards by the research team to minimise these risks. This assessment includes a description of the data lifecycle, an analysis of the necessity and proportionality of the processing, identification of threats and an assessment of inherent risk.

The research team included the following undertakings in the DPIA:

To use a dedicated computer system for data processing. Data will be stored in folders with restricted access to researchers on the corporate servers of the Regional Government of Andalusia. At no time will it be classified or stored in the cloud. No personal data will leave the corporate network of Regional Government of Andalusia.To use the data only for research financed with public funds and carried out by a team of researchers from public bodies belonging to the Andalusian Health System.To maintain patient confidentiality at all times, with researchers and those responsible for statistical analysis handling anonymised data at all times.It will not be considered necessary or feasible to request informed consent from the patient due to the large volume of data to be handled.The transfer of data between PHS-A and research team will be carried out by means of file transfer protocols between health ring servers belonging to the corporate network of the Regional Government of Andalusia. The research project team does not anticipate assignment or transfer of data to third parties.There is a formal commitment not to seek to identify patients from encrypted or anonymised files.All folders and files containing study data in the computer systems will be destroyed once the study has ended.The Principal Investigator undertakes not to transfer data to third parties during the processing of the same.

## Strengths and limitations

### Limitations

The main limitation of the study is the information source itself, since the health records may be incomplete and underreporting may occur due to any of the following: random or accidental errors that are impossible to control for; systematic errors deriving from faulty measuring instruments, the observer, and so on; errors due to the patient being unable to remember all symptoms; errors due to incorrect descriptions of symptoms or diagnoses; errors due to professionals making a diagnosis without having all the information, or a lack of resources, or because the same resources are not available at all centres; classification or coding errors (of events or diagnoses); errors due to confusion (age, etc.); errors due to diagnostic tests giving false positives or false negatives and errors due to imprecise information due to non-quantifiable data (pain, improvement, etc.).

Secondly, this is a retrospective observational study based on real data from clinical practice, so that selection biases may be expected, more specifically, in the selection of OAC treatment, given that DOACs are subject to authorisation prior to dispensing, and dosage depends in turn on renal function, with different adjustments depending on the DOAC. Likewise, there may be differences in the use of acenocoumarol (vs warfarin) depending on the hospital reference area of the patient. This issue will be addressed by a cohort analysis matched by propensity score for treatment.

Thirdly, dabigatran was the first DOAC to be marketed and apixaban and edoxaban the last ones. We will address this problem by matching patients based on their PS and defining the follow-up period once these drugs were marketed.

There are other limitations. It is assumed that the medication dispensed is the medication that is taken by the patient, as it has been considered by other investigators [10, 13, 14, 16] but it cannot be rule out residual confounding. There may however be cases in which the patient obtains medication without a prescription or in a different region from the one in which the study is being conducted (Andalusia). It is not possible to record other medications with a bleeding risk that the patient may be taking that do not require a prescription (such as Aspirin®). However, the use of acetylsalicylic acid will be analysed, and other use of this drug is not expected to have a direct impact on the analysis. Socio-economic status will not be assessed since this data is barely reflected in the clinical records of patients. However, given that DOACs are subject to approval for the indication of non-valvular AF and that this is a universal public health service, socioeconomic status is not expected to affect the selection of type of anticoagulant. Finally, the analysis will be conducted in a particular region in southern Spain and may not extrapolate to other populations.

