**Methods and analysis:**

Population-based retrospective cohort study using RWD from actual practice. Period: January 2012-December 2020. Inclusion criteria: patients with AF who had not taken OACs in the previous 12 months. Exclusion criteria: <40 years, with severe mitral stenosis, or valvular heart disease or aortic and/or mitral valve procedures. Data source: The Andalusian Population Health Database, Spain. Outcome measures: a) Effectiveness: ischaemic stroke, transient ischaemic attack, systemic and pulmonary embolism, and death; b) Safety: gastrointestinal and intracranial haemorrhaging; Independent variables: age, sex, comorbidities, medication and health resource use, CHA_2_DS_2_-VAS_C_, HAS-BLED, and analytical tests. Statistical analysis: crude incidence analysis, survival models, Kaplan-Meier, Cox regression analysis adjusted for possible confounding and paired analysis by propensity score matching.

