### Population and setting

The study will be carried out in the region of Andalusia, where the Public Health System of Andalusia) (PHS-A) provides health coverage to a population of 8.4 million inhabitants.

The patients in the study will be those seen in consultations at any level of health care of the PHS-A (primary care and hospital) between January 2012 and December 2020 (Fig 1) who meet the following inclusion/exclusion criteria:

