### Outcome measures

The pre-specified effectiveness outcomes will be the incidence of new diagnosis among the following list: transient ischaemic attack, systemic embolism, pulmonary embolism, ischaemic stroke and all-cause mortality, as a combined effectiveness endpoint.

Safety outcomes will be the incidence of new diagnosis of major haemorrhages leading to hospital admission (gastrointestinal and intracranial haemorrhages). They will be considered as a combined safety endpoint. Post-traumatic bleeding will be excluded.

All effectiveness and safety events will be associated with their dates of onset and identified using the corresponding International Classification of Diseases (ICD-9 or ICD-10 codes) (S2 Table).

Time-to-event will be defined as the number of days elapsed from the date of initiation of treatment (dispensing at pharmacy) until the date of the event, death or the end of study period (December/2020).

The following independent variables will be analysed according to relevance and availability in PHS-A databases:

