Univariate survival analysis (for time-censored data) will be performed using Kaplan-Meier curves to represent the frequency of occurrence of different events or diseases over time and, where appropriate, in relation to different categories of a variable (age groups, sex, province, etc.) [18].

Survival probabilities, median and quartiles will be calculated, generating statistics and plotting survival functions for each study group.

The log-rank test will be used to test the equality of survival time distributions between different groups.

A preliminary univariate analysis will be performed to identify variables related to time-to-event occurrence (comparing event incidence density to person time to follow-up for different categories of variables).

To analyze this database, confounding variables identified in previous studies will be taken into account. Statistical analyses will include bivariate analysis (association between type of anticoagulant used and each of the other study variables); the Mantel-Haenszel test (analysis stratified by a third variable), as well as multivariate analysis.

A multivariate survival analysis will be performed using Cox proportional hazards or time-dependent Cox regression to control for the effect of confounding variables in the study. Cox regression will be used to create time-to-event models, considering both categorical and continuous predictor variables (covariates) as hypothetical predictors. Potential confounding variables include: age, sex, contacts with health service, comorbidities, concomitant medications, CHA2DS2-VASC and HAS-BLED scores, and previous ischemic and bleeding events.

Determination of the risk of outcomes among DOACs or warfarin versus acenocoumarol (reference) users will be obtained by calculating the specific instantaneous risk ratios for each comparison (Hazard Ratio) (HR) using multivariate Cox regression models. Adjusted survival curves will be used to represent how event risks will evolve over time after adjusting for different confounding variables.

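### The rule for staggered market entry restricts the follow-up period but not the initiation date, and neither initiation period nor reference hospital is named as an adjustment variable

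*Protocol article*

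**What the plan says.** All statements are in the protocol article.

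- **Limitations**, on market timing: "dabigatran was the first DOAC to be marketed and apixaban and edoxaban the last ones". The remedy is: "We will address this problem by matching patients based on their PS and defining the follow-up period once these drugs were marketed". No launch dates are given.
- **Population and setting**: patients are those seen "between January 2012 and December 2020". The same window applies to every cohort, including the acenocoumarol reference. The inclusion criteria admit only patients newly starting an OAC, after 12 months without one.
- **Outcome measures**: time to event is "the number of days elapsed from the date of initiation of treatment (dispensing at pharmacy) until the date of the event, death or the end", the last of these being December 2020.
- **Data analysis plan**, in the Cox regression paragraph: "Potential confounding variables include: age, sex, contacts with health service, comorbidities, concomitant medications, CHA2DS2-VASC and HAS-BLED scores, and previous ischemic and bleeding events". The covariates of the propensity score (PS) are not listed anywhere.
- **Limitations**, on selection of treatment: there may be "differences in the use of acenocoumarol (vs warfarin) depending on the hospital reference area of the patient", and for the DOACs "dosage depends in turn on renal function". PS matching is offered as the answer to this too.
- **Outcome measures**, independent variables: Health Management Area, reference hospital and province are collected. Renal failure codes are collected for HAS-BLED. The abstract's list of independent variables ends with "and analytical tests".

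**The concern.** When drugs enter a market one after another, a valid new-user comparison needs both arms to start treatment in the same calendar period. That is a rule about initiation dates. The article states a rule about follow-up instead, and it does not say how that rule fits with follow-up that begins at dispensing.

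The comparisons most exposed are those of the later DOACs with acenocoumarol, whose users can have started at any time from January 2012. All-cause death is part of the effectiveness composite, so any selection on survival acts directly on the endpoint.

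The PS is the other half of the stated remedy. The article relies on it for market timing and for hospital area, yet the one list of confounders it prints names neither. A PS built from that list alone could not balance them.

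**Working it through.** The article gives no sample size, event count, launch date or expected hazard ratio, so there is no figure to reproduce. The check is a comparison of statements, followed by an illustration.

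**Step 1. What the rule does to a patient who started acenocoumarol in 2012, in the comparison with a DOAC launched later**

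| Reading | Effect | Agrees with the rest of the article? |
|---|---|---|
| Follow-up starts at the DOAC's launch | The patient enters only if still alive, after years of treatment | No: conflicts with time zero in Outcome measures and with the new-user criterion |
| Time zero stays at dispensing | The rule has no effect on this patient, who can be matched to a user of the later drug | Yes, but the market-timing problem is left unsolved |
| Follow-up period is loose wording for entry period | The patient is excluded from this comparison | Yes, and sound, but not what is written |

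**Step 2. Selection drivers named under Limitations, against the confounder list**

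| Driver | Collected? | In the list? |
|---|---|---|
| Market timing (initiation date) | Yes, as treatment start date | Not named |
| Hospital reference area (acenocoumarol vs warfarin) | Yes | Not named |
| Renal function (tied to dosage) | Diagnosis codes; laboratory tests per the abstract | Through HAS-BLED and perhaps comorbidities; no laboratory value |

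The plan also screens Cox covariates by a univariate test at 0.15 against time to event. A variable that drives drug choice therefore has no assured place in that model.

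**Step 3. Simple arithmetic, all inputs assumed**

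*Literal reading.* Suppose a launch 4 years after January 2012 and annual mortality q. The share of the earliest starters who die before launch is 1 − (1 − q)^4:
- q = 0.05: 0.185
- q = 0.07: 0.252
- q = 0.10: 0.344

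Averaged over starters spread evenly across those 4 years, the share is 1 − [1 − (1 − q)^4] / [−4 ln(1 − q)], which gives 0.096, 0.132 and 0.184. These are shares of patients lost, not bias in a hazard ratio.

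*Dispensing reading.* Suppose event rates fall by r a year and mean start dates differ by 3 years. Calendar time alone then gives a ratio of (1 − r)^3:
- r = 0.01: 0.970
- r = 0.02: 0.941
- r = 0.04: 0.885

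The two calculations belong to different readings and cannot be combined.

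**Step 4. Illustration with a true ratio of 1**

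Assumed inputs: a 9-year study; launch at year 2, 4 or 5; uniform initiation; hazard 0.08 × exp(b × c) per person-year, where c is years since January 2012 and b is 0 or −0.05; and the hazard in the first year of treatment multiplied by k = 1, 1.5 or 2. The output is the crude event rate on the later drug divided by that on acenocoumarol. Results for launch at year 5:

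| b | k | No restriction | Follow-up restricted only | Initiation restricted in both arms |
|---|---|---|---|---|
| 0 | 1 | 1.00 | 1.00 | 1.00 |
| 0 | 1.5 | 1.10 | 1.13 | 1.00 |
| 0 | 2 | 1.17 | 1.25 | 1.00 |
| −0.05 | 1 | 0.91 | 0.97 | 1.00 |
| −0.05 | 1.5 | 1.00 | 1.11 | 1.00 |
| −0.05 | 2 | 1.06 | 1.22 | 1.00 |

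Launch at year 2 or 4 stays inside these ranges: 0.93 to 1.12 with no restriction, and 0.97 to 1.18 with follow-up restricted only. The last column is 1.00 by construction, because both arms then share one uniform distribution of start dates. In practice those distributions would differ even after launch, so initiation period still has to be balanced.

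**The case against.** The strongest reply is that the operative sections already describe a new-user design: only new starters are eligible, time runs from dispensing, and patients are classified by first OAC after a 12-month washout. On that view the Limitations sentence merely limits entry to the post-launch period. This reading is possible, and a reader who inferred that the plan is a prevalent-user design would go too far, since that holds only if the sentence overrides the definition of time zero. What stands is that no sentence restricts initiation dates, and the one given restricts something else.

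A reader might also infer that the PS omits calendar time, hospital and renal function. The article does not show this:

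- The list is open-ended and belongs to the Cox model. PS covariates may be set out in a document not shown.
- Saying that PS matching will handle hospital area points towards including it.
- Renal function is not absent. Coded renal failure enters through HAS-BLED and perhaps comorbidities, and the text ties renal function to dosage, not directly to choice of drug. A laboratory value would be an improvement, not the correction of an error.

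Nor does the article support saying that warfarin versus acenocoumarol would mostly compare hospitals. It says only that differences by area may exist.

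Finally, every figure above rests on assumed inputs. The rate ratios are crude. A Cox model on time since initiation with delayed entry would remove part of the duration effect, though not the calendar trend.

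**Conclusion.** The concern holds in this form: the article identifies staggered market entry as a source of bias, and the remedy it writes down does not remove it. On the literal reading the rule contradicts the article's own time zero and new-user criterion. On the reading that keeps time zero at dispensing, it leaves early acenocoumarol starters matchable to users of later drugs. Only a reading that the text does not state solves the problem. In addition, neither initiation period nor reference hospital or area is named for adjustment, although the PS is relied on for both. Whether the PS actually leaves them out is not established.

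The size and direction of any bias cannot be determined from the document. Under the assumed inputs with no true effect, crude ratios fell on both sides of 1: 0.97 to 1.25 with follow-up alone restricted, and 0.91 to 1.17 with no restriction. Because the direction depends on the launch date, the calendar trend and the early hazard, readers could not correct for it afterwards. The renal point is secondary.

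**What to change.** 1. Reconcile the Limitations sentence with Outcome measures. For each pairwise comparison, include in both arms only patients whose first dispensing falls on or after the market entry in Andalusia of the drug compared with acenocoumarol. Follow each patient from their own first dispensing, and state the entry dates used.
2. Match on initiation period or include it in the PS, for example by year or half-year.
3. Name reference hospital or Health Management Area as a PS covariate.
4. As a secondary improvement, add a renal laboratory value from before first dispensing where available, so that renal function does not enter through diagnosis codes alone.

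The cost is fewer acenocoumarol controls for the late-marketed drugs, and possibly thin overlap within hospitals for warfarin. Start date and hospital are already collected, so items 1 to 3 need no new data. Item 4 depends on how complete the laboratory records are.

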### Strengths

The PHS-A serves the vast majority of the Andalusian population, so that coverage of the system can be considered to be population-based. The study will make it possible to analyse a large sample of patients under real rather than ideal conditions (clinical trials), thereby allowing for extrapolation to the general population (high external validity).

To our knowledge, this will be one of the first studies to incorporate RWD to evaluate the effectiveness and safety of medicines in Andalusia. The methodology and knowledge gained can be extrapolated to studies involving other therapeutic groups and researchers.

The study using RWD will make it possible to establish clinically relevant associations, to identify adverse reactions to OACs at an early stage and to consider patient stratification to improve treatment response.

We highlight the long follow-up time for the analysis of events associated with the effectiveness and safety of OACs, as well as the absence of conflicts of interest, as there is no funding from the pharmaceutical industry.

The study researchers constitute a multidisciplinary group, which will make it possible to carry out an exhaustive analysis of the results and to draw conclusions from different healthcare perspectives, to ensure better implementation of the recommendations in routine clinical practice.
